### Data management

All collected data will be entered directly into predetermined files. Checking missing data, out of range values, illogical and invalid responses, will ensure data quality.

### Statistical analysis

The inter- and intra-examiner reproducibility for assessing the primary outcome and secondary outcome OVD measurements will be calculated using a weighted Kappa test.

#### Primary outcome

To verify the survival rate of treatments, as well as to evaluate the survival rate of the teeth examined, we will use a Kaplan-Meier survival analysis and the log-rank test. To evaluate the association between the outcome and patient variables we will use Cox regression test. The significance level for all analyses will be *p* <0.05.

#### Secondary outcomes

The Kolmogorov-Smirnov and Levene tests will be used to consider the normality distribution and homoscedasticity of the data, respectively. Depending on the data distribution, the Mann-Whitney test or *t* test will be applied to compare the degrees of discomfort, perception and concerns related to dental appearance reported by the child and their parents/caregivers; the child and their parent/caregivers’ reported acceptance of treatments among the two groups of intervention, as well as to evaluate the difference in mean scores of CPQ and P-CPQ among the two groups of intervention. The differences between the mean scores of the responses from the CPQ and P-CPQ questionnaire obtained at 1 month and at baseline will be calculated and tested, using a paired *t* test. The Friedman test will be used to compare the changes with regards to concerns related to dental appearance reported by the child and their parents/caregivers, changes in OVD; plaque index and gingival health. To evaluate the association between the secondary outcomes and children variables Ordinal Logistic Regression Analysis will be used. For cost-effectiveness analysis, the primary measure will be the survival rate of treatments. Therefore, as previously mentioned, the ICER will be generated per treatment group by dividing the average initial cost by the survival after 3 years:$$ ICER=\left({\mathrm{cost}}_i-{\mathrm{effectiveness}}_i\right)/\left({\mathrm{cost}}_c-{\mathrm{effectiveness}}_c\right)\mathrm{where}\;i=\mathrm{intervention}\ \mathrm{and}\;c=\mathrm{control}. $$

The significance level for all analyses will be *p* <0.05.

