### Secondary outcomes evaluation

For the assessment of discomfort, the Wong-Baker FACES pain rating scale, an ordinal six-point scale ranging from 0 to 5, will be used [28]. A score of 0 shows a smiling face, indicating no discomfort, whereas a score of 5 shows a crying and sad face, indicating great discomfort. This method has been validated for the assessment of pain and discomfort in children, before and after treatments [28, 29].

To evaluate the perception and concerns related to dental appearance, the Child’s and Parent’s Questionnaire about Teeth Appearance [30] will be used and applied through an interview with children in the school, as well as being filled out by their parents/caregivers at home. This instrument has a version for children and a version for their parents, including questions related to physical, psychological and social order, beyond the perceptions of color change and other esthetic conditions related to the child’s teeth. The questionnaire has five questions with the first three items assessing how the child felt uncomfortable (physical domain of the concept of health), concerned (psychological domain) and avoided smiling (social field) due to the appearance of his/her teeth. An additional item with four sub-items assesses the perception of children and their parents/caregivers about the appearance, color and health of teeth and the last item assesses the opinion of children and their parents/caregivers regarding the satisfaction with the teeth color.

The questionnaire for the evaluation of acceptance in relation to treatment carried out will be applied through interview with children in the school as well as being filled out by their parents/caregivers at home. These questionnaires are based on questionnaires used by Bell et al. [31]. They were rewritten in order to be useful for both the ART and the HT (see Additional file 2). A dentist who is fluent in both languages translated the questionnaires from English to Portuguese. The questionnaire for the children contains six items and employs a five-point pictorial Likert scale. The possible responses are: strongly agree, agree, indifferent, disagree and strongly disagree. The parental questionnaire has five questions with the same possible responses.

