### Follow-up examinations

At baseline, the outcome, child discomfort associated with treatment will be recorded:ART group: before and immediately after treatmentHT group (on two occasions): 1 – before and immediately after the placement of a separator when it is used, and 2 – before and immediately after the placement of the PMC

Perceptions and concerns related to dental appearance will be measured before and after treatment – for children and parents.

Questionnaires assessing acceptance of treatment will be given after treatment – for children and parents.

OVD measurement will be carried out before and after treatment.

Plaque index, gingival health, DMFT/dmft scores (before treatment) and the OHRQoL questionnaires will be recorded before treatment – for children and the OHRQoL questionnaire will be given to parents before treatment. Children will be assessed after 1 week, and then after 1, 6, 12, 24 and 36 months. At 1-week follow-up, the outcomes related to treatment evaluation, OVD measurement, plaque index and gingival health will be re-evaluated. At 1 month follow-up, the outcomes related to treatment evaluation, OVD measurement, plaque index and gingival health, DMFT/dmft scores and the questionnaire OHRQoL, will be re-evaluated. At other follow-ups (6, 12, 24 and 36 months), the outcomes related to treatment evaluation, OVD measurement, plaque index and gingival health, DMFT/dmft scores will be re-assessed (Table 6).

**Table 6 Tab6:** Sequence of procedures performed for each recruited participants

		ART group								HT group							
		Baseline		Evaluation						Baseline		Evaluation					
Event	Completed by	Baseline examination appointment	Treatment appointment	1 week	1 month	6 months	12 months	24 months	36 months	Baseline examination appointment	Treatment appointment	1 week	1 month	6 months	12 months	24 months	36 months
Consent/Assent	Dentist/Dental student	X								X							
DMFT/dmft	Dentist/Dental student	X			X	X	X	X	X	X			X	X	X	X	X
Plaque index	Dentist/Dental student	X		X	X	X	X	X	X	X		X	X	X	X	X	X
Gingival health	Dentist/Dental student	X		X	X	X	X	X	X	X		X	X	X	X	X	X
Instructions of oral hygiene/diet	Dentist/Dental student	X								X							
Orthodontic separators	Dentist/Dental student									X							
Treatment	Dentist/Dental student		X								X						
Wong-Baker faces scale (pre/post treatment)	Child		X							X	X						
Questionnaire about teeth appearance (pre/post treatment)	Child/Parent		X			X					X			X			

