Questionnaire about acceptance in relation to treatment	Child/Parent		X								X						
Measurement of OVD	Dentist/Dental student		X*	X	X	X	X	X	X		X*	X	X	X	X	X	X
Perceptions regarding OHRQoL	Child/Parent		X		X						X		X				
Treatment evaluation	Dentist/Dental student			X	X	X	X	X	X				X	X	X	X	X

***OVD will be measured before and immediately after treatment during the treatment appointment in Atraumatic Restorative Treatment (ART) and Hall Technique (HT) groups

*DMFT/dmft* decayed, missing, filled teeth in permanent teeth/decayed, missing, filled teeth in primary teeth, *OHRQoL* oral health-related quality of life, *OVD* occlusal-vertical dimension

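### The between-arm CPQ and P-CPQ comparison lets distributional pre-tests choose the test and leaves out the pre-treatment score that the trial collects

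*Protocol article*

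**What the plan says.** The Secondary outcomes part of the Statistical analysis section opens with the pre-tests: "The Kolmogorov-Smirnov and Levene tests will be used to consider the normality distribution and homoscedasticity of the data". The test then follows from their result: "Depending on the data distribution, the Mann-Whitney test or" the t test. This one sentence covers discomfort, concerns about dental appearance, acceptance, and quality of life. For quality of life the aim is worded as "to evaluate the difference in mean scores of CPQ and P-CPQ among the two groups of intervention". No covariate is named.

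The next sentence handles change. The differences between the CPQ and P-CPQ scores "obtained at 1 month and at baseline will be calculated and tested, using a paired" t test. No contrast between arms is attached to it. Friedman tests address change in appearance concerns, occlusal-vertical dimension, plaque and gingival health. Ordinal logistic regression is planned for association between the secondary outcomes and the children's variables.

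On data collection, Follow-up examinations states that "the OHRQoL questionnaires will be recorded before treatment", for children and parents, and Table 6 repeats them at 1 month. Discomfort is recorded "before and immediately after treatment" on a scale that Secondary outcomes evaluation describes as "an ordinal six-point scale ranging from 0 to 5". Appearance is also recorded before and after treatment. Acceptance is recorded only afterwards.

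**The concern.** A t test compares means. Mann-Whitney compares the ordering of two distributions and answers a question about means only under extra conditions, such as a pure shift. When a pre-test picks between them, the data decide which hypothesis is tested and which effect measure fits the p-value. For CPQ and P-CPQ this conflicts with the article's own wording, which sets a difference in mean scores as the target.

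Separately, in a randomised superiority trial the treatment question is the contrast between arms. A paired test of 1 month against baseline shows whether scores moved, not whether they moved more under one technique. The pre-treatment score is in hand for every child and parent who answers the questionnaire, yet it does not enter the stated arm comparison. The trial is sized on survival alone, so the quality-of-life comparison has only the precision that 124 children happen to give.

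**Working it through.** **Base number.** Sample size calculation gives 62 % survival with ART, a 25-point difference (taken as 62 % against 87 %), two-sided 5 %, 80 % power, 103 children, then 124. With 1:1 allocation assumed and Freedman's log-rank formula:
- hazard ratio = ln(0.87)/ln(0.62) = 0.291;
- N = 7.849 × (1.291/0.709)² / 0.255 = 102.2, so 103;
- 103 × 1.2 = 123.6, so 124.

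The plan's figure reproduces. It serves below only as the base of 124, or 62 per arm.

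**Precision left out.** Let r be the correlation between baseline and 1-month score. The article does not give it, so 0.3 to 0.7 is an assumption. Relative to an unadjusted comparison of 1-month means:
- ANCOVA variance factor: 1 − r²
- change-score variance factor: 2(1 − r), with equal variances at both times
- equivalent number of children: 124/(1 − r²)
- difference detectable with 80 % power, unadjusted: (1.960 + 0.842) × √(2/62) = 0.50 SD; with ANCOVA, this times √(1 − r²)

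| r | ANCOVA variance | Reduction | Equivalent children | Change-score variance | Detectable difference | Power at 0.5 SD |
|---|---|---|---|---|---|---|
| unadjusted | 1.00 | – | 124 | – | 0.50 SD | 79.5 % |
| 0.3 | 0.91 | 9 % | 136 | 1.40 | 0.48 SD | 83.1 % |
| 0.5 | 0.75 | 25 % | 165 | 1.00 | 0.44 SD | 89.5 % |
| 0.7 | 0.51 | 49 % | 243 | 0.60 | 0.36 SD | 97.4 % |

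The 0.5 SD effect is also an assumption. With about 51.5 per arm (103 in total, after loss), power goes from 71.8 % to 75.8 %, 83.4 % and 94.4 %.

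**Which test the pre-test picks.** I simulated 3,000 trials per case with 52 per arm. Mann-Whitney was used if Kolmogorov-Smirnov rejected normality in either arm or Levene rejected equal variance. The article does not state how the pre-tests combine, nor whether the Kolmogorov-Smirnov test carries the Lilliefors correction for estimated parameters, so both versions were run. Score shapes are assumed.

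| Score shape | Mann-Whitney chosen, plain | Mann-Whitney chosen, Lilliefors |
|---|---|---|
| Gamma, shape 3 (skewness 2/√3 = 1.15) | 14 % | 85 % |
| Gamma, shape 1.5 (skewness 2/√1.5 = 1.63) | 41 % | 99 % |
| Skewed six-level scale, 0 to 5 | 100 % | 100 % |

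For a single sample of 62 with skewness 1, normality was rejected in about 3 % (plain) or 46 % (Lilliefors).

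**Does the choice matter?** With identical distributions in both arms, the two-stage rule rejected in 4.1 % to 5.7 % of trials, so its size holds. With equal means but different shapes (gamma with shape 1 against shape 6, both with mean 20), the t test rejected in 6.4 %, Mann-Whitney in 44.8 % and the two-stage rule in 44.1 %. That case was built to show the mechanism. It is not a forecast for this trial.

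**The case against.** **An unadjusted comparison is valid, and covariate adjustment is usually left to the full plan.** The first half is right: randomisation makes the unadjusted contrast unbiased, and the loss is one of precision only. The second half would hold if the article were silent. It is not: it names the tests, the rule that picks them, and a separate use for the baseline.

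**The wording may mean change scores compared between arms.** No time point is given in that clause, so this reading is possible. It does not remove the point, because 2(1 − r) − (1 − r²) = (1 − r)², which is never negative. ANCOVA is therefore at least as precise, and at r = 0.3 a change score is worse than ignoring the baseline.

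**Other analyses already use baselines.** The paired and Friedman tests do, but within children. The ordinal regression is worded for association with the children's variables and is not stated to give an adjusted arm effect.

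**Stronger readings that a reader might infer, and that are not supported:**
- That the two-stage rule inflates type I error. The simulation shows that it does not when the distributions are identical.
- That the choice of test for CPQ and P-CPQ is close to a coin toss. The simulated frequency of Mann-Whitney runs from low to nearly certain, depending on assumed skewness and an unstated version of the test, and the article gives no CPQ distribution.
- That the data choose the hypothesis for every secondary outcome. For the 0 to 5 discomfort scale and the Likert items, the pre-test mostly leads to Mann-Whitney anyway, so the practical harm there is small.
- That all collected baselines are ignored. Acceptance has none, and others enter the within-child tests.

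**Conclusion.** The point holds for the quality-of-life comparison, as a modest improvement that needs no new data. Two features are fixed in the text: a data-driven choice between tests of different hypotheses under a target worded as a difference in means, and an arm comparison with no stated place for the pre-treatment score. The first makes the tested quantity uncertain without raising the false-positive rate under identical distributions. The second costs a share r² of the variance: 9 %, 25 % or 49 % at r = 0.3, 0.5 or 0.7.

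These figures rest on an assumed correlation, 1:1 allocation and a roughly linear relation between baseline and 1-month scores. They compare ANCOVA with an unadjusted comparison of means, not with Mann-Whitney. The primary log-rank analysis and the sample size are unaffected.

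**What to change.** Replace the pre-test rule with one named analysis per outcome:

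- **CPQ and P-CPQ:** ANCOVA of the 1-month score on arm and baseline score, with robust standard errors, reporting the adjusted mean difference and its confidence interval. Robust standard errors remove the need for a Levene step. Keep the paired t test as a description of change.
- **Discomfort and appearance:** a proportional-odds model with arm and the pre-treatment score. A standard Mann-Whitney test takes no covariate, so it should not be left as an alternative here. As the HT arm has two discomfort occasions, the wording should say which one is compared with ART.
- **Acceptance:** the Mann-Whitney test, as no baseline exists.

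Delete the Kolmogorov-Smirnov and Levene pre-tests as selectors of the test. The measurements needed are already in the schedule in Table 6, so the only cost is a change in analysis wording, best made before outcome data by arm are examined.

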## Discussion

This trial aims to investigate which minimally invasive treatment applicable outwith the dental surgery setting, the HT or ART, has the best survival rate for occluso-proximal cavitated lesions in primary molars when applied in a low-technology setting. In addition, we aim to answer the question: how do these treatments compare for child self-reported discomfort associated with treatment, pain and infection rates, OVD changes, incremental cost-effectiveness, DMFT, DMFT/dmft changes, OHRQoL, perceptions, concerns and acceptance related to dental appearance reported by children and their parent/caregivers?

ART was developed approximately 30 years ago and involves the use of manual instruments to prepare cavities, followed by placement of a high-viscosity GIC [3]. This strategy for the management of caries has been tested in many settings with good outcomes for single surfaces [5, 6, 39]. However, the survival rate of ART for occluso-proximal lesions is low [13, 14]. As a result of this reduced longevity, there is some resistance within the dental and scientific community to recommending this technique for everyday use [40].

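### OVD, plaque index and gingival health are given only a within-child Friedman test, so no ART-versus-HT comparison is specified for them; the CPQ and P-CPQ arm comparison is not stated to use the baseline score

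*Protocol article*

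**What the plan says.** The Secondary outcomes part of the Statistical analysis section of the protocol article assigns tests to outcomes by name.

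- **Between arms.** Either a Mann-Whitney or a t procedure: this "test will be applied to compare the degrees of discomfort, perception and concerns related to dental appearance reported by the child and their parents/caregivers". Acceptance of treatment is covered in that sentence too, which closes "as well as to evaluate the difference in mean scores of CPQ and P-CPQ among the two groups of intervention".
- **CPQ and P-CPQ change.** Scores on each "questionnaire obtained at 1 month and at baseline will be calculated and tested, using a paired" t test.
- **Repeated occasions.** One sentence starts "The Friedman test will be used to compare the changes with regards to concerns related to dental appearance reported by the child", adds the parents' reports, and ends with "changes in OVD; plaque index and gingival health".
- **Regression.** "To evaluate the association between the secondary outcomes and children variables Ordinal Logistic Regression Analysis will be used".

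Study design describes a two-arm, parallel-group superiority trial. The Discussion asks "how do these treatments compare for child self-reported discomfort associated with treatment, pain and infection rates, OVD changes". Follow-up examinations and Table 6 show that OVD, plaque, gingival health and OHRQoL are all recorded before treatment and again afterwards.

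**The concern.** OVD, plaque index and gingival health are absent from the list of outcomes compared between the two groups. The one test attached to them by name looks at change across occasions within children. If the analysis follows this text, a significant result would show only that values move over time. Over 36 months, in children aged 6 to 8 at entry, that could happen equally in both arms. A real difference between HT and ART could go untested.

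A smaller matter concerns CPQ and P-CPQ. The arms are compared, but the text does not say that the baseline score enters that comparison, and the change from baseline is tested only within children. Precision that the trial has already paid for may be lost.

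**Working it through.** **1. Which test goes with which outcome**

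| Outcome | Between-arm test named | Within-child test named |
|---|---|---|
| Discomfort, acceptance | Mann-Whitney or t | none |
| Appearance concerns | Mann-Whitney or t | Friedman |
| CPQ, P-CPQ | Mann-Whitney or t | paired t, 1 month against baseline |
| OVD | none | Friedman |
| Plaque index, gingival health | none | Friedman |

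**2. What the Friedman test can detect**

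With n children and k occasions, each child's values are ranked across occasions. The statistic is 12/(nk(k+1)) × ΣR_j² − 3n(k+1), where R_j is the rank sum at occasion j. Allocation does not enter.

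**3. Illustrative simulation**

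The inputs are assumptions, not figures from the documents: 50 children per arm, normal data, within-child correlation 0.5, baseline plus three visits, 2,000 runs, two-sided 5% level. The shifts shown apply at every post-baseline visit. ANCOVA and the t test compare the arms at the last visit, with and without baseline. Entries are the percentage of runs that reject.

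| Shift in arms 1 and 2 (SD) | Friedman, pooled | Friedman, arm 1 / arm 2 | ANCOVA | t test, no baseline |
|---|---|---|---|---|
| +0.5 and +0.5 (no arm difference) | 99.75 | 87.8 / 89.4 | 4.9 | 4.8 |
| +0.25 and −0.25 | 4.35 | 29.95 / 31.15 | 81.85 | 71.2 |
| 0 and +0.5 | 53.7 | 5.9 / 88.9 | 80.1 | 68.1 |

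The pooled Friedman test nearly always rejects when the arms do not differ, and rejects at about the nominal level when they move apart. Running it in each arm separately does not repair this: significance in one arm and not in the other is not a test of the difference.

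**4. Missed visits**

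The standard Friedman test needs every occasion for every child. OVD has eight occasions: before and after treatment, then six follow-ups. If attendance at each follow-up were independent, the share with complete data would be:

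- 95% per visit: 0.95^6 = 0.735, or 91 of 124 children
- 90% per visit: 0.90^6 = 0.531, or 66 of 124 children

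Both attendance rates are assumed. The protocol's own planning figures imply 103/124 = 83% retained. Dropout that persists once it starts would cost fewer complete records than the independent case.

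**5. Baseline adjustment for CPQ and P-CPQ**

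Relative to comparing 1-month scores alone, ANCOVA multiplies the variance of the arm contrast by about 1 − r², where r is the correlation between baseline and 1-month score. The documents give no r.

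- r = 0.3: 0.91, a 9% reduction
- r = 0.5: 0.75, a 25% reduction
- r = 0.7: 0.51, a 49% reduction

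**6. The sample size is not touched**

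No stated figure rests on the secondary tests. The planned number reproduces with the Freedman log-rank formula, taking 62% against 87% and assuming 1:1 allocation. HR = ln 0.87 / ln 0.62 = 0.291, which needs 26.06 events. Dividing by the mean event probability of 0.255 gives 102.2, so 103; and 103 × 1.2 = 123.6, so 124.

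**The case against.** Several points can fairly be made for the plan.

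- **OVD has a longitudinal aim.** The Discussion also sets out to learn whether the occlusion re-establishes after crown cementation. A repeated-measures test within the HT arm suits that. This stands, and it is a reason to keep the Friedman test. It does not supply the comparison of OVD changes that the Discussion also asks for.
- **Plaque and gingival health are not in the Discussion's list of comparisons.** True. Their comparative purpose follows from the two-arm superiority design and their place among the secondary outcomes in the Abstract.
- **The regression might include allocation.** Its covariates are not listed, so arm is neither named nor excluded. The Abstract lists the secondary tests collectively and does not say that any is exclusive. Both leave room for an arm comparison, but neither specifies one.
- **An analysis plan, not shown, may add detail.** That answers a silence. Here the article names a specific test that does not match the question, and a plan that follows it inherits the mismatch.
- **An unadjusted randomised comparison is valid.** It is. Baseline adjustment for CPQ and P-CPQ is a gain in precision, not the repair of an error.

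A reader might infer more than the text supports: that CPQ and P-CPQ, appearance or discomfort lack an arm comparison, or that baseline values are ignored. The section gives all of these outcomes a Mann-Whitney or t test between the groups, and the paired t test uses the baseline score. DMFT/dmft has no test named at all, but in a condensed article that is an omission, not a wrong choice.

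**Conclusion.** For OVD, plaque index and gingival health the point holds. The only test named is within-child and cannot answer how ART and HT compare. This follows from the form of the test and does not depend on the simulation, whose percentages illustrate it under assumed inputs. The loss of children with a missed visit is also a property of the standard test; its size depends on attendance, and the 91 and 66 of 124 are illustrations only.

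For CPQ and P-CPQ the point is narrower. A between-arm test exists, it is not stated to use the baseline score, and the possible gain of 9% to 49% in variance rests on assumed correlations of 0.3 to 0.7.

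Only secondary outcomes are affected. The primary log-rank analysis and the 124 children stand.

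**What to change.** **OVD, plaque index, gingival health.** Name as the between-arm analysis a mixed or GEE model with arm, visit, arm-by-visit and the pre-treatment value. Use an ordinal link where the score is ordinal, as for the 0–2 plaque and 0–3 gingival scores on the treated tooth. Report the HT minus ART difference at each visit (on the link scale where one is used) with its confidence interval. Such a model also keeps children with incomplete visits.

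**Friedman test.** Keep it for within-arm change, in particular whether the occlusion re-establishes after crown placement, and say that it is not the comparison of arms.

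**CPQ and P-CPQ.** Compare arms by ANCOVA of the 1-month score on arm and baseline score. Keep the paired t test as a within-arm description.

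**Cost.** A change of wording in the analysis section and slightly more analysis work. All the data are already scheduled for collection. The change should be fixed before outcome data are examined by arm.

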### Sample size calculation

The sample size was calculated based on the primary outcome – treatment survival, using the log-rank test in survival analysis. This involved a two-tailed test based on survival rate reported for ART (62 %) [13] after 2 years of follow- up, using the absolute difference of 25 % between groups, *α* of 5 % and power (strength) of 80 %. This gave an estimate of 103 children (with one tooth each treated within the study) to be recruited. After increasing by 20 % to compensate for participant loss to follow-up, the final sample size was set at 124 children (and 124 teeth).

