
### Data analyses

Outcome data for the trial will be analyzed as intention-to-treat (ITT) so that all participants randomized and all events will be accounted for in the primary analysis. However, if (1) more than 10 % of children cannot tolerate either one or both of the treatments at the time of treatment, or (2) there is a difference greater than 20% in the dropouts between the arms (therefore raising the index of suspicion that there is a problem with tolerance of the treatments or other problem with delivery), we will also carry out an “on treatment” (also known as per-protocol) analysis and interpret the differences between ITT and “on treatment” appropriately.

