**Fig. 2 Fig2:**
[figure not shown]
Method for measuring occlusal-vertical dimension (OVD) using a probe with markings at 1, 3, 6, and 9 mm

Plaque [33] and gingival bleeding indices [34] will be recorded on the treated tooth as well as obtained by averaging the measurements from seven index teeth [22] (Table 4).

**Table 4 Tab4:** Evaluation criteria for the assessment of plaque index [33] and gingival health [34]

Plaque index scores [33]	• 0: no plaque • 1: thin visible plaque, difficult to identify • 2: thick visible plaque, easily detected.
Gingival health scores [34]	• 0: Normal: the gingival tissue appears firm, with pinkish or pale pink and opaque surface, with thin margins and variable degree of stippling. Contact with millimeter probe show its firmness • 1: slight inflammation: the gingival margin has slight change of color (reddish or bluish red) and is slightly swollen. Does not bleed after gentle probing • 2: moderate inflammation: the gingival tissue has become swollen (rounded edge, or bright red/blue). There is bleeding after gentle probing; 3: severe inflammation: the gingival tissue has markedly red or bluish red, swollen and enlarged, with ulcerations. Tendency to spontaneous bleeding

For the assessment of changes in DMFT/dmft, the same criteria for the evaluation of caries presence used at the baseline evaluation will be used [25] and the DMFT and dmft will be recorded [26].

An incremental cost-effectiveness ratio (ICER) will be calculated. The average cost per treatment will be quantified for both ART and the HT. Effectiveness will be measured by percentage of treatment survival. A microcosting will be carried out to estimate the direct costs of treating children with ART or the HT. This will include the capital costs of all equipment and instruments, materials and overheads, and the costs of time and labor. Additionally, the procedures will be timed using a stopwatch, started when the child has his/her mouth open and the operator is about to start the restorative intervention and stopped when the child stands up from the treatment table. The initial cost of treatments will be calculated, taking into account the parameters described in the Table 5. Therefore, the initial costs of treatments will be calculated by summing the expenses of capital cost, material cost and labor cost [35]. The ICER will be generated per treatment group by dividing the average initial cost by the survival after 3 years:

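### The Friedman test named for OVD, plaque and gingival health drops any child with a missed occasion, and for treated-tooth scores drops children partly by loss of the tooth

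*Protocol article*

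**What the plan says.** The Statistical analysis section, under Secondary outcomes, reads "The Friedman test will be used to compare the changes with regards to concerns related to dental appearance reported by the child" (and by parents or caregivers), and the sentence goes on to "changes in OVD; plaque index and gingival health". It does not limit the occasions to be compared and does not say what happens to a child with a gap.

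The schedule comes from Follow-up examinations and Table 6: "Children will be assessed after 1 week, and then after 1, 6, 12, 24 and 36 months".

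- **OVD:** before treatment, immediately after it, and at six visits, so 8 occasions.
- **Plaque index and gingival health:** baseline and six visits, so 7 occasions.
- **Appearance:** "Perceptions and concerns related to dental appearance will be measured before and after treatment", with a 6-month administration added in Table 6, so at most 3 occasions.

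The sites of measurement differ. Under Secondary outcomes evaluation, plaque and "gingival bleeding indices [34] will be recorded on the treated tooth" and are also averaged over seven index teeth. OVD is read on the canines, with the first primary molars used only when no canines are present.

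Loss is expected: "After increasing by 20 % to compensate for participant loss to follow-up", the target became 124 children. Table 3 lists pulp disease needing pulpotomy or extraction as a Major Failure and counts an exfoliated tooth as a Success.

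**The concern.** The Friedman test orders each child's readings from first to last occasion and needs all of them. A child with one gap contributes nothing, not even at the visits attended. Over seven or eight occasions in three years, that discards much of the data that were collected.

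The loss matters most for OVD. The Discussion criticises an earlier study for having only 8 children at 30 days, promises fuller capture, and says the trial will test whether the occlusion re-establishes after crown cementation. The readings that bear on this are the early ones. A test over all occasions throws them away for any child who is absent later, for whatever reason.

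For plaque and gingival scores on the treated tooth there is a second mechanism. No score exists once the tooth has been extracted or shed, so a complete series to 36 months consists only of teeth that stayed. Extraction can follow a Major Failure and exfoliation counts as Success, so the retained set is shaped partly by tooth loss. The trial is designed around a 25-point difference in treatment survival, so the retained set could differ between arms.

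This point concerns only who enters the test. That the Friedman test contains no arm term is a separate matter.

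**Working it through.** **The plan's own figure.** The protocol gives no sample size for the Friedman analyses. Its overall figure reproduces: 103 × 1.2 = 123.6, rounded up to 124.

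**Inputs from the protocol:** 124 children; a 20 % allowance for loss; six follow-up visits, of which five precede 36 months.

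**Inputs assumed, because the protocol gives none:** a proportion m of 3 to 5 % missed at each of those five visits; a proportion q of treated teeth extracted or shed before 36 months, from 0 to 40 %; pre-treatment and treatment-day readings complete; the three sources of loss independent.

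**Formula:** complete series = 124 × (1 − 0.20) × (1 − q) × (1 − m)^5

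**Step 1, loss alone:** 124 × 0.80 = 99.2, so at most 99 children.

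**Step 2, with missed visits, q = 0** (OVD and the seven-tooth means):
- m = 3 %: 99.2 × 0.97^5 = 99.2 × 0.859 = 85
- m = 5 %: 99.2 × 0.95^5 = 99.2 × 0.774 = 77

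If the OVD reading immediately after treatment can also be missed in 5 %, the exponent becomes 6 and OVD keeps 99.2 × 0.95^6 = 73.

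**Step 3, treated-tooth plaque and gingival scores only:**

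| Teeth lost (assumed) | m = 3 % | m = 5 % |
|---|---|---|
| 0 % | 85 | 77 |
| 20 % | 68 | 61 |
| 40 % | 51 | 46 |

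**Step 4, what is discarded.** At the same m, and with little permanent loss in the first week, 124 × 0.97 = 120 or 124 × 0.95 = 118 children have a 1-week reading. Against 85 and 77 complete series, valid 1-week readings from about 35 to 41 children go unused for OVD and the index means.

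**Step 5, sensitivity.** The 20 % is stated as an increase, not as a loss rate. If loss only brings 124 back to 103, step 2 gives 103 × 0.859 = 88 and 103 × 0.774 = 80. If missed visits cluster in the same children, the counts rise towards the step 1 ceiling. If 10 % of each visit is missed, step 2 falls to 99.2 × 0.90^5 = 59.

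**Appearance for comparison.** With 2, 5 or 10 % missing at each of its two later occasions, 124 × 0.98², 124 × 0.95² and 124 × 0.90² give 119, 112 and 100.

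**The case against.** The strongest reply is that the protocol does not say which occasions enter the test. A Friedman test limited to the visits up to 1 month would lose few children and would answer the OVD question. Choice of occasions and handling of gaps are often settled in an analysis plan, which is not shown here. This stands to the extent that the figures above are conditional on using all scheduled occasions. It does not dispose of the point. The protocol names the test for changes in outcomes it follows to 36 months and sets no limit, and a plan that keeps this test can avoid the deletion only by imputing or by giving up later visits.

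A second reply is that no method can supply scores for a tooth that is gone. That is true: late treated-tooth results describe the remaining teeth under any analysis. What can be recovered is the earlier readings of teeth lost later.

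Several stronger readings are tempting, and the protocol does not support them:

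- *A contradiction with intention-to-treat.* The Data analyses section ties its commitment that "all participants randomized and all events will be accounted for in the primary analysis" to the primary analysis, which is Kaplan-Meier with the log-rank test. It does not promise that every randomised child enters every secondary test.
- *The treated tooth must be present for all four outcomes.* Appearance is a questionnaire, OVD is normally read on canines, and the seven-tooth mean does not as such depend on the treated tooth. The fallback to first primary molars could involve the treated tooth in some children only.
- *Appearance suffers the 36-month loss.* It ends at 6 months at the latest.
- *The set is selected on the primary outcome.* The composite includes Minor Failures, which do not in themselves remove a tooth. Not every Major Failure leads to extraction, and exfoliation is a Success. Selection is on physical loss of the tooth, which is only partly related to the primary outcome.

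**Conclusion.** The point holds for OVD, plaque index and gingival health. If the named test is run over the scheduled occasions, at most 99 of 124 children enter at 20 % loss, and about 77 to 85 with 3 to 5 % of each earlier visit missed. For treated-tooth plaque and gingival scores alone, the count is about 61 to 68 if 20 % of teeth are lost, and 46 to 85 over the full assumed range. In that last set, exclusion depends partly on tooth loss and may differ by arm; the protocol gives no figure from which to size such a difference. The missed-visit and tooth-loss rates are assumptions; only the 124 and the 20 % come from the protocol. Appearance is little affected, and the primary analysis is untouched.

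**What to change.** For OVD, plaque index and gingival health, replace the Friedman test with a repeated-measures analysis that uses every available visit, with visit as a factor:

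- a linear mixed model for OVD and the seven-tooth means;
- an ordinal mixed model or GEE for scores on the treated tooth;
- the Skillings-Mack test, which accepts incomplete blocks, if a rank test is preferred.

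Treat treated-tooth readings as ended, not missing, once the tooth is lost, and report the number of teeth contributing per arm at each visit.

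The cost is a change of wording and some programming; no new data are needed. The downside is reliance on assumptions about missing data. The likelihood-based models assume data missing at random given earlier visits, while GEE and Skillings-Mack need stronger conditions. Late treated-tooth results will still describe only the teeth that remain, and the report should say so.
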